#### Clinical Presentation and Program Fit

To determine whether students will be a good fit for the U-PEACE program, members of the research team will conduct a modified version of the Diagnostic Interview for Anxiety, Mood, and OCD-Related Neuropsychiatric Disorders: Child and Adolescent Version (DIAMOND-KID) [65] with preliminarily eligible adolescents at baseline. The DIAMOND-KID is a semistructured diagnostic interview and self-report screener assessing clinically significant mental health concerns from the *Diagnostic and Statistical Manual of Mental Disorders, Fifth Edition* [65]. The DIAMOND-KID has demonstrated very good to excellent test-retest reliability and good convergent validity with youth aged between 10 and 17 years [65]. Inter-rater reliability on most diagnoses was found to be good to very good—except for anxiety and depressive disorders, in which inter-rater reliability was found to be questionable in youth, possibly due to inconsistent reporting of the specific duration and timing of symptoms by youth [65]. All DIAMOND-KID assessments will take place in person, on school campuses; and each assessment is expected to take about 1 hour.

#### Demographics and Service Use

Self-reported demographic information of students, caregivers, and coaches will be collected. Demographic characteristics will include contact information, age, race and ethnicity, self-reported gender, and sexual orientation. In addition, students will be asked to report on any past or current psychiatric or psychological services, as well as any past or current psychiatric medications. At each time point following baseline, students will be asked to update previously reported service and medication information. It is anticipated that both English and Spanish speaking students will be included in the RCT.

#### Academic Progress

Student grade point average for each academic quarter will be calculated by converting all grades to a 5-point scale (4.0=A to 0.0=F). Student grades will not be weighted. School attendance will be collected as measured by the number of days a student was present in school for the academic year. Both student grade point averages and attendance records will be collected in person by having students log into their web-based academic portals and share the pertinent information with study coordinators.

Academic problems will also be measured using the AAPC [69]. The AAPC is a 24-item teacher-report measure that assesses adolescents’ concerns in the classroom (eg, behavioral withdrawal and class disruptions). Items are rated on a 4-point Likert-type scale that ranges from “not at all” to “very much,” with higher scores suggesting more severe classroom concerns. The AAPC has demonstrated excellent internal consistency (0.92) and strong concurrent validity in assessing behaviors associated with academic functioning [69]. The AAPC will be distributed to teachers chosen by their respective students, with the same teacher completing the form for the same student throughout the study.

#### Anxiety and Depression Symptoms

Adolescents’ anxiety symptoms will be measured using the Generalized Anxiety Disorder 7-item Scale (GAD-7) [61]. The GAD-7 will be used as both a self- and caregiver-report measure; the items in it are rated on a 4-point Likert-type scale that ranges from “not at all” to “nearly every day,” with higher scores suggesting more severe anxiety symptoms. While the authors are not aware of published psychometric properties on the parent-report GAD-7, the self-report GAD-7 has demonstrated good reliability in adolescent populations (Cronbach α=0.88) and has demonstrated strict measurement invariance by adolescents’ sex and grade, as well as good convergent and discriminant validity [62,79].

Adolescents’ depression symptoms will be measured using the PHQ-9 [59]. Items on the PHQ-9 scale are rated on a 4-point Likert-type scale that ranges from “not at all” to “nearly every day,” with higher scores suggesting more severe depression symptoms. The PHQ-9 has demonstrated good internal reliability (McDonald Ω=0.87) among adolescents, and confirmatory factor analysis for a 1D model suggested adequate fit [80].

There may be instances in which the research team chooses to administer a modified version of the PHQ-9 to adolescents and their caregivers. For instance, given that this measure may be administered remotely without the presence of a study team member, the Patient Health Questionnaire-8 (PHQ-8) may be used to ensure that any suicide-related concerns are handled immediately and in person by the research team [60]. Research has suggested that omitting the suicide item on the PHQ-9 has minimal impact on scoring [81]. The correlation between the PHQ-9 and PHQ-8 remains high; therefore, the cutoff scores remain unchanged [60,81]. While the authors are not aware of published psychometrics for parent-report PHQ-8, research on the general population suggests good sensitivity and specificity [60].

In addition to the GAD-7 and PHQ-9, adolescents’ anxiety and depression symptoms will also be measured by the Revised Children’s Anxiety and Depression Scale–Short-Form (RCADS-SF) [70]. The RCADS-SF is only used as a self-report measure in this study. The 25 items in it are rated on a 4-point Likert-type scale that ranges from “never” to “always,” with higher scores suggesting more severe symptoms of anxiety and/or depression. The RCADS-SF has demonstrated adequate reliability and acceptable discriminant validity in comparison to the 47-item RCADS [70].

#### Anxiety-Based Impact on Academic Functioning

The impact of adolescents’ anxiety symptoms on their academic functioning will be measured by the Child Anxiety Impact Scale–Academic Subscale (CAIS-AS) [66,67]. The CAIS-AS will be used as a self- and caregiver-report measure. The 10 items in the subscale are rated on a 4-point Likert-type scale that ranges from “not at all” to “very much,” with higher scores suggesting more anxiety-based academic impairment. The CAIS-AS child report has demonstrated excellent internal consistency (0.82) and good construct validity. Similarly, the parent report exhibited very good internal consistency (0.85) and good construct validity [67].

#### Irritability

Adolescents’ irritability will be measured using the Affective Reactivity Index (ARI) [68]. The ARI will be used as a self- and caregiver-report measure. The 7 items in it are rated on a 3-point Likert-type scale that ranges from “not true” to “certainly true,” with higher scores suggesting more irritability. The ARI has demonstrated good to excellent internal consistency in both the caregiver-report and the youth self-report versions [68].

#### Internalizing and Externalizing Symptoms

Adolescents’ internalizing and externalizing symptoms will be measured using the Behavior and Feelings Survey (BFS) [71]. The BFS is only used as a self-report measure in this study [71]; it is a brief 12-item scale that ranges from “not a problem” to “very big problem,” with higher scores suggesting more severe internalizing and/or externalizing symptoms. The BFS has demonstrated good internal consistency (0.87) and strong discriminant validity [71].

#### Distress Tolerance

Adolescents’ emotional distress tolerance will be measured using the Distress Tolerance Scale (DTS) [74]. The DTS is only used as a self-report measure in this study. The 15 items in it are rated on a 5-point Likert-type scale that ranges from “strongly disagree” to “strongly agree,” with higher scores suggesting lower distress tolerance. The DTS has generally demonstrated adequate to good internal consistency (0.72-0.82) [74], and its factor structure was upheld in a validation study with children and adolescents [82].

#### Acculturation

Adolescents’ acculturative experiences will be documented using the Abbreviated Multidimensional Acculturation Scale (AMAS-ZABB) [73]. The AMAS-ZABB is a 42-item self-report measure that assesses cultural identity, language competence, and cultural competence related to acculturation in the United States and individuals’ country of origin (as applicable). Items are rated on a 4-point Likert-type scale that ranges from “strongly disagree” to “strongly agree.” While the AMAS-ZABB has been validated in some adult populations, the scale is yet to be validated in adolescents [83]. The AMAS-ZABB will be distributed to all participating students at the 4 major time points during phase 2 and only administered at baseline during phase 3 of the study.

#### Discrimination

Adolescents’ experiences of discrimination will be measured using the Everyday Discrimination Scale (EDS) [72]. In addition to assessing discrimination experiences, the EDS also assesses unfair treatment and perceived reasons for such treatment (eg, race and sexual orientation). The EDS is a 10-item self-report measure and is rated on 6-point Likert-type scale that ranges from “never” to “almost every day,” with higher scores suggesting more frequent experiences of discrimination. Although the EDS was not originally created for adolescents, the scale has been used previously in studies with adolescent participants [84].

#### Treatment Progress

Adolescents will identify 3 problems they want to target during the study using the Top Problems Assessment [75]. The Top Problems Assessment is a personalized change measure used extensively with the UP-A to assess change over time in client-derived reasons for treatment. The Top Problems Assessment has demonstrated criterion validity, test-retest reliability, and sensitivity to change with youth aged between 7 and 13 years [75]. Although the authors are unaware of a validation study of Top Problems with adolescents, Top Problems has been used with adolescent clients receiving the UP-A in prior research [85]. In this study, adolescents will provide a score of 0 to 10, with 10 being the most severe, at all 4 major time points and each program session.

#### Adherence and Fidelity

U-PEACE adherence will be measured through adolescents’ attendance in the program. Session attendance will be recorded through a single item on a clinician-reported or research team member-reported measure. Attendance at individual meetings with the program coach will also be recorded through a single item on coach-reported documentation. Homework completion will be measured through a single item on a clinician-reported measure for each treatment session. Treatment progress, attendance, and homework completion measures will only be completed by students who are randomized to the U-PEACE group. Clinician fidelity to the U-PEACE protocol will be evaluated through audio recordings or live coding by a research associate for assessment of program fidelity, upon obtaining consent from participants.

#### Therapeutic Alliance and Program Satisfaction

Adolescents’ rapport with their program leaders will be measured using the Therapeutic Alliance Scale for Children–Revised (TASC-R) [76,77]. The TASC-R is a 12-item self-report measure of therapeutic alliance. Items are rated on a 4-point Likert-type scale that ranges from “not at all” to “very much,” with higher scores suggesting a stronger therapeutic alliance. The TASC-R has been used to assess alliance in various studies, including CBT for anxiety in youth [86].

Adolescents’ satisfaction with the U-PEACE program will be measured using the Client Satisfaction Questionnaire (CSQ) [78]. The CSQ is an 8-item self-report measure of client program satisfaction, client self-efficacy, and likelihood of recommending the program to others. Items are rated on a 4-point Likert-type scale, with higher scores suggesting higher client satisfaction. The CSQ demonstrated excellent internal consistency and good convergent validity with other similar measures administered to adolescents [87,88]. Therapeutic alliance and program satisfaction measures will only be completed by students who are randomized to the U-PEACE group.

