### School-Based Interventions for Youth Anxiety and Depression

Mental health professionals can address these barriers by meeting adolescents where they naturally are and delivering evidence-based mental health services in community settings—such as high schools [17,19-21]. The existing research on school-based interventions for anxiety and depression is primarily focused on increasing access to care, health promotion, and prevention [22-25]. Consequently, school-based interventions have made it possible to deliver mental health care to millions of children who likely would not have received care outside of this setting [26]. Furthermore, school-based services offer the opportunity for mental health professionals to fulfill the mental health needs of children and adolescents through training of school staff [27], increasing prevention efforts [18,24], and reduction of stigma associated with mental health issues [28].

However, while many of these interventions are found to be effective, effect sizes with school-based samples are typically smaller than those with clinic-based samples, and they are often not statistically significant in comparison to clinic-based settings [29-31]. Smaller effect sizes may, in part, be due to the challenges that mental health professionals have faced when adapting and implementing these EBTs into community settings [31-33]. Particularly, there may be school-specific barriers to implementing and sustaining some components of interventions that are more traditionally offered in clinics, such as exposures [33]. These may include financial (eg, purchase materials and pay for staff), attitudinal (eg, support of other school staff), and logistical (eg, competing school priorities) barriers that further compound misalignment between the goals of an EBT and a school’s values and focus [34]. Consequently, specific components of EBTs may not be applied with fidelity—or may be deimplemented by stakeholders altogether, given the school-specific barriers—reducing the effectiveness of the interventions [35]. Some of these implementation challenges may be mitigated by using a transdiagnostic intervention that can address a wide range of mental health concerns [36].

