### Measures

#### Overview

Each U-PEACE and SAU group will have 4 assessment time points (baseline, midpoint, after completion, and 1-month follow-up) of questionnaire administration. Detailed information regarding questionnaire administration at each time point can be found in Table 2.

**Table 2 table2:** List of assessment measures and time points.

Measure name	Every session	Baseline	Midpoint	After completion	1-month follow-up
Demographic survey	N/A^a^	Adolescent and parent or caregiver	N/A	N/A	N/A
DIAMOND-KID^b^–full interview [65]	N/A	Adolescent	N/A	N/A	N/A
DIAMOND-KID–initial interview [65]	N/A	Adolescent^c^	N/A	N/A	N/A
DIAMOND-KID–self-report scanner [65]	N/A	Adolescent^d^	Adolescent^d^	Adolescent^d^	Adolescent^d^
Service Utilization Form	N/A	Adolescent^d^	Adolescent^d^	Adolescent^d^	Adolescent^d^
Generalized Anxiety Disorder 7-item Scale [61]	N/A	Adolescent and parent or caregiver	Adolescent and parent or caregiver	Adolescent and parent or caregiver	Adolescent and parent or caregiver
Child Anxiety Interference Scale–Academic Subscale [66,67]	N/A	Adolescent and parent or caregiver	Adolescent and parent or caregiver	Adolescent and parent or caregiver	Adolescent and parent or caregiver
Patient Health Questionnaire-9 [59]	N/A	Adolescent and parent or caregiver	Adolescent and parent or caregiver	Adolescent and parent or caregiver	Adolescent^e^ and parent or caregiver
Affective Reactivity Index [68]	N/A	Adolescent and parent or caregiver	Adolescent and parent or caregiver	Adolescent and parent or caregiver	Adolescent and parent or caregiver
Adolescent Academic Problems Checklist [69]	N/A	Teacher	Teacher	Teacher	Teacher
The Revised Children’s Anxiety and Depression Scale–Short-Form [70]	N/A	Adolescent^d^	Adolescent^d^	Adolescent^d^	Adolescent^d^
Behavior and Feelings Survey [71]	N/A	Adolescent^d^	Adolescent^d^	Adolescent^d^	Adolescent^d^
School achievement (as measured by attendance and report card)	N/A	Adolescent^d^	N/A	Adolescent^d^	Adolescent^d^
Everyday Discrimination Scale [72]	N/A	Adolescent	Adolescent	Adolescent	Adolescent
Abbreviated Multidimensional Acculturation Scale [73]	N/A	Adolescent	Adolescent^c^	Adolescent^c^	Adolescent^c^
Distress Tolerance Scale [74]	N/A	Adolescent	Adolescent	Adolescent	Adolescent
Top problems [75]	Adolescent	Adolescent	Adolescent	Adolescent	Adolescent
Participant adherence	Clinician	N/A	N/A	N/A	N/A
Therapeutic Alliance Scale for Children–Revised [76,77]	N/A	N/A	Adolescent	N/A	N/A

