Client Satisfaction Questionnaire [78]	N/A	N/A	Adolescent	N/A	N/A

^a^N/A: not applicable.

^b^DIAMOND-KID: Diagnostic Interview for Anxiety, Mood, and OCD-Related Neuropsychiatric Disorders: Child and Adolescent Version—Full Interview.

^c^Not administered at these time points in the randomized controlled trial.

^d^Measure was only administered during the randomized controlled trial.

^e^Patient Health Questionnaire-8 was used at 1 month.

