#### Quantitative Analyses

Quantitative analyses will be conducted to assess (1) within-participant treatment-related changes in emotion regulation and symptoms after participation in U-PEACE and (2) implementation outcomes, including treatment fidelity, acceptability, and implementation costs. We will examine missing data patterns, attrition rates, and distributional properties of measures and use transformations when necessary. Depending on patterns of missing data, analyses may use full maximum likelihood estimation, multiple imputation, and inclusion of covariates related to missingness to account for missing data.

Reliable change indices (RCIs) will be calculated by dividing the within-respondent differences in self-report and caregiver scores (ie, anxiety symptoms, depression symptoms, irritability, anxiety-related impairment, and academic problems) from baseline to after treatment by the SE for each measure [92]. RCI has previously yielded reliable estimates of clinically significant change over the course of treatment and can successfully analyze small sample sizes [93]. RCI >1.96 indicates clinically significant change throughout the course of the program—which would provide preliminary support that U-PEACE is impacting theoretical mechanisms and participants’ outcomes.

Furthermore, multilevel models will be evaluated to consider nesting of repeated measures (3 or 4 time points, depending on the measure) within participants, who are further nested within study conditions. School and U-PEACE group provider or providers will be included as predictors of intercept and slope to control for environmental differences between the groups. The best-fitting model for change over time will be determined for each dependent variable based on the Akaike Information Criterion and Bayesian Information Criterion. Time will be coded in weeks and will be “centered” alternately at treatment follow-up, such that model intercepts will represent mean scores at these assessments [94]. Treatment condition (ie, U-PEACE or SAU) will be entered as a predictor of the level 2 growth curve parameters (intercepts and slopes). These models will be used to assess group differences in both purported mechanisms of change (ie, emotion regulation measures) and in program outcomes (ie, symptom measures, academic outcomes, and diagnostic measures) as evidenced by slope or mean level differences at different time points.

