#### Mixed Methods Analyses

Qualitative feedback, individual participant response to treatment, and treatment implementation measures from the case series will be interpreted together to elucidate the association between how experiences and perceptions of U-PEACE vary by treatment outcome and implementation. This information will be used to modify U-PEACE before the implementation of the RCT. RQA [89,90,95] will be used to quickly and efficiently summarize qualitative feedback from participants and community members throughout the trial. A joint display analysis will be developed following best practices [96]. The joint display will simultaneously illustrate individual quantitative (eg, emotion regulation, diagnostic symptomatology such as depression and anxiety, and culturally relevant outcomes such as experiences of discrimination) and qualitative (eg, themes and quotes) results reflecting participants’ experiences of U-PEACE. Likewise, we will simultaneously examine quantitative (eg, fidelity) and qualitative (eg, themes) implementation data to guide protocol changes before the RCT; these changes will be aimed to increase U-PEACE feasibility and appropriateness.

For the RCT, patterns in the quantitative outcome and implementation data will be examined to generate specific questions for the qualitative interviews after the RCT. Multilevel modeling will be used to elucidate treatment response classifications and will be used to ensure an appropriate representation of adolescent and caregiver participation in the interviews. The resulting joint display will compare representative interview quotes across key domains (eg, intervention acceptability and tolerability) and implementation indicators (eg, U-PEACE fidelity and alliance) between those classified into 2 aggregated clusters: nonresponders, which consists of those identified as falling within the deteriorated or unchanged categories, versus responders, which will include participants whose scores fall within the improved or recovered categories. Inclusion of implementation outcomes (ie, fidelity to treatment, treatment adherence, and acceptability) will provide insight into the sustainability of U-PEACE in diverse high school settings.

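### The Client Satisfaction Questionnaire is scheduled at midpoint only, so the quantitative acceptability result cannot describe the completed U-PEACE program

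*Protocol article*

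**What the plan says.** The section on therapeutic alliance and program satisfaction names the scale: "Adolescents’ satisfaction with the U-PEACE program will be measured using the Client Satisfaction Questionnaire (CSQ"). It describes eight items on satisfaction, self-efficacy and willingness to recommend the program. It gives no time point but limits who answers: "Therapeutic alliance and program satisfaction measures will only be completed by students who are randomized to the U-PEACE group".

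The timing is in Table 2. Its columns are "Measure name Every session Baseline Midpoint After completion 1-month follow-up", and the row reads "Client Satisfaction Questionnaire [78] N/A N/A Adolescent N/A N/A". The scale is therefore given at midpoint and at no other visit. The row carries no footnote that would change this for the randomized phase.

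The Quantitative Analyses section lists "implementation outcomes, including treatment fidelity, acceptability, and implementation costs" among the things to be assessed. Mixed Methods Analyses then relies on acceptability: "Inclusion of implementation outcomes (ie, fidelity to treatment, treatment adherence, and acceptability) will provide insight into the sustainability of U-PEACE". The section on potential implications also promises information on the program's acceptability.

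**The concern.** A satisfaction score taken halfway describes only the half that the student has attended. Dissatisfaction that arises later cannot appear in it, and neither can satisfaction that grows as skills are practised. Followed as written, the plan would report quantitative acceptability of U-PEACE from mid-program ratings. The joint display would set those ratings beside interviews held at the end of participation and beside response categories that use change from baseline to after treatment.

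The timing may matter more if the later modules differ in kind from the earlier ones. In the parent program, situational exposure is module 7 of 8. The introduction gives exposures as an example of a component that may be hard to deliver in schools: "there may be school-specific barriers to implementing and sustaining some components of interventions that are more traditionally offered in clinics, such as exposures".

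**Working it through.** The plan gives no figure to reproduce here. The check is a reading of the schedule and a count of sessions.

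**Schedule.** Table 2 has five time columns: every session, baseline, midpoint, after completion, and 1-month follow-up. The satisfaction row has an entry in the third column only. No other standardized satisfaction or acceptability scale is listed.

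**Where midpoint falls.** The Study Intervention section expects U-PEACE to have a session count in the parent program's range of 12 to 16. Assuming that midpoint means half of the sessions:

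- 12 / 2 = 6 and 16 / 2 = 8, so the rating falls around session 6 to 8.
- 12 − 6 = 6 and 16 − 8 = 8, so 6 to 8 sessions remain unrated.

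**Where situational exposure falls.** Table 1 recommends these session counts for modules 1 to 6 of the parent program: 1–2, 2–3, 1–2, 1–2, 2–3, 1–2.

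- Minimum: 1 + 2 + 1 + 1 + 2 + 1 = 8, so module 7 starts at session 9 at the earliest.
- Maximum: 2 + 3 + 2 + 2 + 3 + 2 = 14, so module 7 could start as late as session 15 if every module ran to its upper count.

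On the parent program's order, a rating at session 6 to 8 therefore precedes modules 7 and 8 in every case.

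**What comes before the rating.** Table 1 puts behavioral experiments in module 3 and exercises that provoke physical sensations in module 4.

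- At minimum counts, modules 1 to 4 take 1 + 2 + 1 + 1 = 5 sessions, so both are finished before session 6.
- At maximum counts, modules 1 and 2 take 2 + 3 = 5 sessions, so module 3 starts at session 6. Module 4 starts at 5 + 2 + 1 = session 8.
- Module 6 has generalized emotion exposures. At minimum counts it falls in session 8, at the edge of the midpoint range.

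Some exposure-type work may therefore come before the rating. Situational exposure does not.

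**Other sources on acceptability.**

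- *Interviews.* The Iterative Feedback section plans interviews of some U-PEACE participants and their caregivers at the end of participation, evenly divided between responders and nonresponders. The sample size section sets a target of 25. It does not say how many of the 25 are adolescents. The joint display names acceptability and tolerability as a domain.
- *Attendance and homework.* These are recorded by session, but the Mixed Methods section lists adherence and acceptability as separate outcomes.

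**Schedule against analysis.** The Quantitative Analyses section plans multilevel models, of the kind it has already described, to compare this questionnaire across study conditions. Those models use 3 or 4 repeated measurements per participant. The schedule supplies one measurement, in one arm. Neither a growth curve nor a between-arm contrast can be fitted. The Therapeutic Alliance Scale has the same schedule and the same restriction.

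**The case against.** The strongest reply is that the design is mixed-methods and does not rest acceptability on one scale. End-of-program interviews address it directly, and attendance and homework cover the late sessions. The article's stated objective concerns feasibility and scalability, and acceptability is one implementation outcome among several. No sentence makes the questionnaire the sole measure of it. A midpoint score also has a use of its own, since it captures students before they drop out.

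Much of this stands, and it rules out some stronger readings that a reader might infer:

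- *That the trial cannot answer whether the whole program is acceptable.* The interviews can speak to that, although in a subset and without an arm-wide score.
- *That the introduction identifies exposures as the hardest component.* It says that there may be barriers to some components and gives exposures as an example. It ranks nothing. The barriers it lists are financial, attitudinal and logistical, and a student satisfaction scale would not capture most of them.
- *That students meet no exposure work before the rating.* The module content shows otherwise.
- *That situational exposure certainly follows the rating in U-PEACE.* The article allows modules to be added or removed, and it defines neither the adapted order nor midpoint.

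The reply does not supply a standardized score for the completed program. Adherence is not acceptability on the article's own list, and interviews in a subset give no quantitative summary of the arm.

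**Conclusion.** The point holds in a limited form. The only standardized satisfaction measure is taken at midpoint, so the quantitative acceptability result describes the program up to that visit and not the completed program. This follows from Table 2 alone and needs no assumption about module order. Whole-program acceptability then rests on end-of-program interviews in a subset (target 25), supported by adherence data.

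The size depends on two assumptions. If midpoint is half of 12 to 16 sessions, 6 to 8 sessions go unrated. If U-PEACE also keeps the parent program's order, the unrated part includes all of situational exposure, from session 9 at the earliest.

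A named implementation outcome is affected. The comparison of U-PEACE with services as usual on symptoms and academic outcomes is not. The planned between-condition analysis of the questionnaire is a separate contradiction and cannot be carried out as described.

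**What to change.** **If collection is open.**

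1. In the Table 2 satisfaction row, keep midpoint and add the after-completion visit for U-PEACE students. State both time points in the section on therapeutic alliance and program satisfaction.
2. In the Quantitative Analyses section, make the after-completion score the quantitative acceptability outcome. Summarize it descriptively within the U-PEACE arm, with the number of students who answered.
3. Report the midpoint scores of students who left before completion on a separate line, not pooled with the later scores.

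**If collection is closed.** The abstract says that it ended in May 2025, while the Results section describes aim 3 collection as under way. If it has ended, label the result mid-program satisfaction and base conclusions about the whole program on the end-of-program interviews.

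**In either case.** Remove the multilevel comparison of the questionnaire across conditions, or reconcile it with the restriction to the U-PEACE arm. A second time point does not repair it, because the comparison arm still has no score. The therapeutic alliance measure needs the same correction. If the Table 2 row is a misprint, correct the row.

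**Cost.** Eight items are added to a visit that already takes place and for which students receive US $50. The questionnaire becomes slightly longer. Students who drop out will lack the later score, so it will describe those who stayed; the separate line for early leavers makes this visible.
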